## Abstract

**Background:**

The burden of urinary incontinence (UI) on the American public is great. The impact of this condition will only continue to rise as the population ages, yet the quality of care provided at the primary care level has been inadequate to date. The Optimizing Primary Care Tools for Incontinence MAnagement (OPTIMA) study has been designed as a four-pronged, practice-based incontinence intervention aimed at improving the management of UI by primary care providers (PCP).

**Methods:**

In this pragmatic cluster randomized controlled trial, providers across four Southern California healthcare systems are randomized at the office level to receive incontinence intervention (*n* = 24 offices; 72 providers) vs. a non-intervention routine primary care cohort (*n* = 24 offices; 72 providers). The intervention includes (i) academic detailing with physician education and individual performance feedback; (ii) clinical decision support with note templates, order sets, and pop-up EHR alerts; (iii) access to co-management with a dedicated advanced practice provider; and (iv) implementation of an electronic referral service in which a specialist screens referrals for appropriateness. To achieve adequate power, the study will require 720 patients (360 patients per arm, average of 15 patients per office).

The primary provider outcome is the quality of UI care, as measured by adherence to a set of 13 quality indicators (QIs) on a 6-month chart review. Secondary provider outcomes include specialty referral rates (overall specialist referrals and presence of appropriate delay of referral) and disease-specific knowledge measured by the Pelvic Floor Awareness and Knowledge Survey (PFAKS). Patient self-reported outcomes include disease-specific knowledge measured by PFAKS, UI severity measured by the International Consultation on Incontinence Questionnaire (ICIQ-SF) and Urinary Distress Inventory (UDI-6), UI response to therapy measured by Patient Global Impression of Improvement (PGI-I), and patient-perceived shared decision making via the 9-item Shared Decision Making Questionnaire (SDM-Q-9). Patient outcomes are measured at baseline, 3-, and 6-month timepoints post-appointment with the study provider.

**Discussion:**

We expect this study to determine the efficacy and impact of comprehensive practice-based interventions on provider quality for UI care.

**Trial registration:**

The study is registered at ClinicalTrials.gov (NCT05534412). Registered on August 1, 2022.

## Administrative information

Note: the numbers in curly brackets in this protocol refer to SPIRIT checklist item numbers. The order of the items has been modified to group similar items (see http://www.equator-network.org/reporting-guidelines/spirit-2013-statement-defining-standard-protocol-items-for-clinical-trials/).

**Table Taba:** 

Title {1}	*O*ptimizing *P*rimary Care *T*ools for *I*ncontinence *MA*nagement (OPTIMA): protocol for a cluster randomized controlled trial
Trial registration {2a and 2b}.	The study is registered at clinicaltrials.gov (NCT05534412). Registered on August 1, 2022.
Protocol version {3}	Feb 20, 2025, v77
Funding {4}	This trial is funded by the Agency for Healthcare Research and Quality (AHRQ)

Role of sponsor {5c}	The sponsor maintains authority over all aspects of the trial including design, management, interpretation of results, and publication.

## Introduction

### Background and rationale {6a}

Urinary incontinence (UI) is defined by the International Continence Society as the complaint of any involuntary leakage of urine [1]. According to the National Health and Nutrition Examination Survey, the prevalence of UI among adult women ranges from 38% to 53% [2, 3]. With the aging population, it is projected that the number of women with UI will increase by 55% between the years 2010 and 2050 [4]. UI negatively impacts health-related quality of life and is particularly associated with embarrassment, stigma, and social isolation [5].

The Assessing Care of Vulnerable Elders (ACOVE) project previously developed indicators of high-quality care for vulnerable community-dwelling elders with UI [6]. Gnanadesigan et al. used these quality indicators (QIs) to measure care among 372 patients identified to be at risk for functional decline [7]. They found that the quality of UI care provided to vulnerable older patients was inadequate. Pelvic examination, an important measure, was performed in only 20% of older women with UI; only 50% of eligible patients received medical treatment for incontinence, and only 13% were prescribed behavioral intervention despite its proven effectiveness [7].

Poor quality of UI care is not unique to older adults. We compared care for the ACOVE population to that provided to 137 younger women with a diagnosis of UI in a hospital-based multi-specialty medical group in Los Angeles. UI care was insufficient in both groups [8]. Younger women, in particular, are more likely to be referred directly to an incontinence specialist — such as a urologist or urogynecologist — without receiving any incontinence care from their primary care provider (PCP) [2]. These factors lead to surgical specialists performing first-line care for UI, which is costly to the healthcare system and reduces access to specialty care for those who need higher-level UI care [9].

### Objectives and trial design {7} {8}

The Optimizing Primary Care Tools for Incontinence MAnagement (OPTIMA) project is a cluster randomized trial of a four-pronged practice-based incontinence intervention conducted across four health systems in Southern California (Fig. 1). It was created in response to the Agency for Healthcare Research and Quality (AHRQ) initiative: Improving Nonsurgical Treatment of Urinary Incontinence among Women in Primary Care (RFA-HS-21-001). The overall goals of the project are to improve primary care management of incontinence, reduce unnecessary referrals to specialists, and improve patient-centered outcomes. Herein, we describe the detailed methods of this clinical trial, which is reported in accordance with the SPIRIT 2013 (Standard Protocol Items: Recommendation for International Trials) guidelines [10].

**Fig. 1 Fig1:**
[figure not shown]
Study schematic and eligibility for practice, provider, and patient participants. Legend: Flowchart to the study with inclusion/exclusion criteria for each level of recruitment, including practice, primary care provider (PCP), and female patient with bothersome urinary incontinence (UI)

## Methods

### Study setting {9}

The present study is a cluster randomized design with a target of 48 offices in Southern California from 4 academic health systems: one private, two public-private, and one public county health system.

### Eligibility criteria {10}

Inclusion and exclusion criteria for each level of recruitment (practice, PCP, and patient) are described in Fig. 1.

### Informed consent {26a} {26b}

Informed consent for PCP cohort is obtained by a member of the study team at respective sites. After single IRB approval was obtained (IRB #802004), the study team obtained a waiver of documented consent and a full HIPAA waiver at each site, allowing patients to self-enroll in the study. In addition, the study team obtained a waiver of informed consent and a partial HIPAA waiver for baseline chart abstraction of prior UI cases.

## Interventions

### Explanation for the choice of comparators {6b}

Eligible practices (i.e., offices) identified by health system and primary care leadership were randomized into intervention and routine care arms (Fig. 1). Office specialties include family medicine, gynecology, geriatrics, and general internal medicine, as they manage women’s primary care and often show a need in the literature for improved UI care.

The comparator is usual (standard-of-care) UI management as delivered at each participating site. Usual care refers to the care that individual clinicians provide based on their individual training. The usual care arm PCPs receive a best practice alert when they open the patient encounter, but no additional UI-specific tools, training, or decision support are provided.

### Intervention description {11a}

The four-pronged, practice-based incontinence intervention includes (1) provider education and training, (2) electronic clinical decision support tools, (3) opportunity for co-management with an advanced practice provider (APP), and (4) access to an electronic referral mechanism in which a specialist screens referrals for appropriateness. Outcomes to be measured include quality of provider care (defined by adherence to urinary incontinence QIs as determined by 6-month chart review) (Table 1), specialist referral rates, and patient-reported outcomes. Practice and PCP timeline detailed in Fig. 2.

**Table 1 Tab1:** Urinary incontinence quality indicators (QIs)

Evidence-based measures of implementation strategies to be used as care guidelines and care measurement tools	Evidence base
*Diagnosis: targeted evaluation/basic history*	
1) A basic history should be obtained from a woman presenting with complaints of new or worsening bothersome UI, including: a) Determining whether stress, urge, or both symptoms are present b) Lifestyle factors (fluid intake) if urge urinary incontinence (UUI) is present 2) History of prior pharmacologic therapy for UI 3) Severity assessment	AUA/SUFU Guideline [11] AHRQ Update [12] Delphi Panel [13]
*Targeted physical exam*	
4) A physical exam should be performed on a woman presenting with complaints of new/worsening bothersome UI symptoms, including a vaginal exam to assess for contributors to UI (fibroids, pelvic organ prolapse) and an assessment of pelvic floor muscle strength (ability to perform Kegel exercises)	LA County DHS SUI Expected Practices Delphi Panel [13]
*Diagnostic testing*	
5) Urinalysis should be performed on a woman who presented with new/worsening bothersome SUI to screen for microhematuria or urinary tract infection	LA County DHS SUI Expected Practices Delphi Panel [13]
*Treatment/management UUI*	
Behavioral therapy 6) A woman who presents with new or worsening bothersome UI should initially be offered pelvic floor muscle training (PFMT)	ACP clinical practice guidelines [14] AUA/SUFU Guideline [11] AHRQ Update [12] Delphi Panel [13] Cochrane review [15]
*Treatment/management of SUI*	
Behavioral therapy 7) A woman who is overweight (BMI > 25) with new or worsening symptoms should be advised to lose weight Pharmacological therapy 8) Anticholinergic or beta agonist therapy should not be offered as a treatment to a woman who presents with new or worsening bothersome SUI without symptoms of OAB	ACP clinical practice guidelines [14] Delphi Panel [13]
*Treatment/management of UUI*	
Pharmacological therapy 9) Anticholinergic or beta agonist therapy may be offered as a treatment to a woman who presents with new or worsening OAB Behavioral therapy 10) If a woman presents with new or worsening bothersome UUI, then a history about fluid intake should be obtained	AUA/SUFU Guideline [11]LA County DHS Expected Practices Delphi Panel [13]
QIs for urinary incontinence (UI) based on those developed by the Assessing Care of Vulnerable Elders (ACOVE) project	

*UUI *urge urinary incontinence, *SUI* stress urinary incontinence, *OAB* overactive bladder

**Fig. 2 Fig2:**
[figure not shown]
SPIRIT diagram of practice and PCP timeline. Legend: Allocation occurs at practice-level prior to PCP enrollment. Timepoint (*t*) at which PCP’s final patient participant is enrolled differs based on individual provider

#### Academic detailing

Enrolled PCPs receive academic detailing prior to patient recruitment. This portion of the intervention integrates principles of Educational Outreach, utilizing stepwise application of evidence-based techniques (i.e., baseline knowledge inventories, targeted interventions, etc.) to improve clinical decision-making [16]. First, PCPs complete their baseline UI knowledge assessment via the Pelvic Floor Awareness and Knowledge Survey (PFAKS), a 31-item validated pelvic floor disorder knowledge questionnaire [17]. Once complete, the study team holds an in-person or virtual lecture at intervention practices. Providers unable to attend receive a one-on-one lecture via Zoom. Lectures are led by a UI clinical champion, either a urologist/urogynecologist or PCP from that site who is part of the research team and has expertise in UI management. The lecture centers on a set of thirteen previously developed and tested quality-of-care indicators (QIs) that cover all aspects of non-surgical management of UI, including history and physical examinations (i.e., pelvic exam), urinalysis, initiation of conservative treatment (i.e., lifestyle/behavioral interventions, pelvic floor training, medication, and when to refer to a UI specialist in urogynecology (Table 1)). The QIs were independently developed using the RAND Appropriateness, or Delphi, Method [13] and are validated for use in a diverse population [8, 18, 19]. PCPs also receive a pocket guide with a treatment algorithm.

Within a month after the lecture, UI specialists provide individualized coaching for intervention PCPs. This includes a one-on-one review of the PCP’s baseline quality of care for UI, as measured by retrospective chart abstraction of up to 5 previous UI encounters. Baseline charts are identified by a diagnosis code for UI (Appendix A). After reviewing prior care, the UI specialist offers individualized recommendations. Intervention PCPs are then ready for patient recruitment. Baseline chart abstraction is also performed in the routine care cohort, although without the individualized coaching sessions.

#### Clinical decision support tools

Clinical decision support (CDS) refers to a range of tools and systems that help healthcare providers make informed decisions about patient care. The study team developed a combination of CDS tools that are implemented into each intervention office’s electronic health record (EHR) system. These included note templates (pre-formatted EHR clinical notes containing text and placeholders that streamline documentation and prompt providers to record and address key clinical information), order sets (pre-configured groups of laboratory tests, medications, and referrals that can be selected together to streamline ordering), and electronic alerts (automated, EHR-based prompts that notify providers when specific clinical criteria are met and suggest appropriate next steps) (Table 2). PCPs are taught how to utilize the CDS tools during the UI lecture.

**Table 2 Tab2:** Clinical decision support tools

Quality indicators for which clinical decision support will be used	Type of clinical decision support
Diagnosis: targeted evaluation/basic history	
Positive screen	*Banner/smart zone*
1–3. Assessment of UI (symptoms and history)	*Templated note*
4. Targeted physical exam	*Templated note*
5. Diagnostic testing (Urinalysis)	*Order set*
6. Pelvic floor muscle exercises	*Templated note and order set for PFMT*
Treatment/management of SUI	
7. Weight loss recommended	*Templated note*
8. Anticholinergic (or beta agonist) therapy should not be offered as a treatment to a woman who presents with new or worsening bothersome SUI without symptoms of overactive bladder (OAB)	*Interruptive alert*
Treatment/management of UUI	
9. History about fluid intake should be obtained	*Templated note*
10. Counseling about behavioral modification, including fluid restriction and bladder training	*Templated note*
11. A woman with UUI/OAB who is prescribed anticholinergic medications should also be counseled about behavioral therapy	*Templated note and order set*
12. Medication (anticholinergics or beta-3 agonists) should be offered when behavioral therapy and PFMT do not control symptoms	*Templated note and order set*
Follow-up after treatment	
13. A woman treated for any form of UI should be re-evaluated within 3 months of initiating intervention for the efficacy and/or complications of any intervention	*Templated note and order set*

Electronic alerts for providers vary by site and include either an interruptive alert or a non-interruptive alert (banner). Electronic alerts are timed to fire within the EHR system during the PCP’s visit with patient participants, alerting the PCP to the patient’s positive screen for bothersome UI. Electronic alerts are the only aspect of the CDS toolset provided to both arms of the study. Since the primary outcome of interest is the quality of UI care provided (and not whether or not a UI-related conversation occurs in the first place), electronic alerts are implemented since embarrassment may contribute to patients’ reluctance to initiate UI conversations.

#### eConsult referrals

The study team implemented an electronic referral system at intervention offices modeled after the participating public county system’s electronic consultation system (eConsult). A specialist in urology or urogynecology triages referrals for appropriateness of care; for referrals where adequate care is not performed (i.e., one or more of the basic QIs for first-line UI care are not met), the reviewing specialist sends a direct message to the PCP with clinical recommendations to consider before referring to the specialist.

#### APP co-management

Intervention PCPs also have the option to refer study patients to an Advanced Practice Provider (APP) co-manager with expertise in UI. If referred, the patient is scheduled for a visit (telemedicine or in-person) with the APP, who provides follow-up teaching and non-surgical management according to standard clinical practice. APPs can also refer participating patients to a urology/urogynecology specialist as clinically indicated.

### Criteria for discontinuing or modifying allocated interventions {11b}

Enrolled PCPs who leave participating practice or health system will be excluded from the study. Patients can request to discontinue participation in the study at any point by informing their PCP and/or a member of the study team.

### Strategies to improve adherence to interventions {11c}

PCPs received a small honorarium for participating. Those who attend the lecture as part of the intervention arm also receive Maintenance of Certification (MOC) credit. PCP clinical champions periodically email the intervention PCPs to inquire about any questions they may have and assess their experience with the intervention toolset. These touchpoints also enable PCPs to discuss barriers and potential issues related to the study or the CDS/referral tools that arise as they see patient participants.

### Relevant concomitant care permitted or prohibited during the trial {11d}

PCPs in both arms manage patient care without prohibitions, including the option of referring to a specialist.

### Provisions for post-trial care {30}

PCPs in routine care offices know they will receive the intervention once their patient participation is complete (delayed intervention). Once the last patient participant for a routine care PCP has reached the 6-month timepoint in the study, routine care providers will be offered access to the intervention tools.

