### Participant timeline {13}

Intervention PCPs receive the academic detailing portion of the intervention prior to patient recruitment. Six-month PFAKS is timed based on their office’s UI lecture (Fig. 3). Patient recruitment opens for intervention PCPs once their individual coaching session (i.e., lecture followed by a review of prior care with a clinical champion) is completed and is closed once 10–13 patients per provider are enrolled; the exact timeline will differ between PCPs based on factors such as their patient population (e.g., proportion eligible) and number of outpatient visits per week. Since routine care PCPs do not receive academic detailing, 6-month PFAKS will be timed based on the enrollment date. Patient recruitment in this arm begins once enrolled PCPs complete the baseline surveys. Both patients and PCPs in the routine care arm complete an identical battery of surveys as those in the intervention arm.

Patient participants are enrolled 1–2 weeks prior to an upcoming appointment with their PCP and complete the baseline survey battery upon enrollment. Patient participation includes the completion of baseline, 3-, and 6-month surveys; a patient is considered finished with the study once they complete the 6-month surveys (Fig. 3).

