## Assignment of interventions: allocation

### Sequence generation {16a}

Offices were assigned to study arms using randomization lists generated using Wei’s Urn method (to allow for equal sample sizes). Randomization at the practice level was done for all four sites by the study biostatistician 1:1 to each study arm, stratified by study site and office specialty (family medicine, gynecology, geriatrics, and general internal medicine), using PASS 2020 software [27]. Physicians working within a given practice received the same designation to prevent cross-contamination of intervention materials.

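### The per-PCP trigger for the delayed intervention lets tools into a control office while colleagues' patients are still being assessed, against the stated reason for office-level randomisation

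*Protocol article*

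**What the plan says.** Provisions for post-trial care {30} sets the trigger for offering the tools to control-arm providers: "Once the last patient participant for a routine care PCP has reached the 6-month timepoint in the study". The sentence before it is also framed around the individual provider: "PCPs in routine care offices know they will receive the intervention once their patient participation is complete (delayed intervention". No condition on the office or on the trial as a whole is stated.

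Sequence generation {16a} gives the reason for one allocation per practice: "Physicians working within a given practice received the same designation to prevent cross-contamination of intervention materials". The Discussion returns to this when it defends the unblinded design. It cites office-level randomisation as limiting routes for contamination and, in the same sentence, cites the delayed intervention.

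On timing, the Fig. 2 legend says that the timepoint "at which PCP’s final patient participant is enrolled differs based on individual provider". For the control arm, Participant timeline {13} says "Patient recruitment in this arm begins once enrolled PCPs complete the baseline surveys", which sets no common start date for an office. Sample size {14} assumes an average of 3 providers per office. Outcomes {12} assesses the primary outcome over 6 months of care for each patient.

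**The concern.** Randomising by office protects the comparison only while the whole control office stays free of the intervention. A trigger tied to one PCP's last patient can end that protection for the office before its other PCPs have finished. A fast-recruiting control PCP could take up the templates, order sets, lecture and pocket guide while a colleague along the corridor is still enrolling or has patients in the assessment window.

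Each PCP's own patients are safe, because release follows their last 6-month timepoint. The exposure falls on colleagues' patients. Any spillover would raise control-arm quality scores and could alter control-arm referral behaviour, which shrinks the primary and referral contrasts. The Discussion presents office-level randomisation and the delayed intervention as two reassurances and does not consider that the second, as written, can weaken the first.

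**Working it through.** **Step 1: does the rule permit overlap?** Count months from the index visit of the first-finishing control PCP's last patient. The Abstract measures timepoints from the appointment, so that PCP qualifies at month 6. Let a colleague's patient in the same office have an index visit at month v. That patient's chart window runs from v to v + 6.

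- v ≤ 0: the window closes by month 6, so there is no overlap.
- 0 < v < 6: the index visit precedes release, and the last v months of the window fall after it. For v = 2, that is 2 of 6 months.
- v ≥ 6: the index visit and the whole window fall after release.

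Overlap therefore occurs for every colleague's patient first seen after the early finisher's last patient. It is full only when the gap reaches 6 months. Most indicators (history, severity, examination, urinalysis, pelvic floor training, weight advice) fit the presenting visit. In the middle case the exposed part is mainly later care, such as the 3-month re-evaluation, medication after behavioural therapy has failed, and referral.

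**Step 2: reproduce the planned sample size.** Inputs from Sample size {14} and the Abstract: difference 6 points, SD 20, alpha 0.05 (two-sided assumed), power 80%, 3 PCPs per office, 15 patients per office (so 15/3 = 5 per PCP), correlation 0.16 within provider and 0.04 within office.

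- Unclustered n per arm = 2 × (1.96 + 0.842)² × 20² / 6², which rounds up to 175.
- Design effect = 1 + (5 − 1) × 0.16 + 5 × (3 − 1) × 0.04 = 1 + 0.64 + 0.40 = 2.04.
- 175 × 2.04 = 357 per arm, or 360 in whole offices of 15. This matches the plan's 360 per arm and 720 in total.
- Standard error at 360 per arm = 20 × √(2 × 2.04 / 360) = 2.129. Power = Φ(6/2.129 − 1.96) = 80.5%.

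The full 6-point contrast is assumed, so nothing is set aside for contamination.

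**Step 3: illustrate dilution.** Let f be the share of control patients exposed and s the share of the effect passed on to them. The contrast becomes 6 × (1 − f × s). The documents give neither f nor s, so both are assumptions.

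| f × s | Example | Contrast (points) | Power at 360 per arm |
|---|---|---|---|
| 0 | release waits for the office | 6.00 | 80.5% |
| 0.025 | 10% exposed, a quarter passed on | 5.85 | 78.5% |
| 0.05 | 10% exposed, half passed on | 5.70 | 76.3% |
| 0.10 | 20% exposed, half passed on | 5.40 | 71.8% |

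**The case against.** The strongest reply is that contamination is possible but not shown. The text says only that access is offered; there are no release dates, uptake figures or evidence of overlap. It also moves from one PCP to routine care providers in the plural, which leaves room for a collective release. PCPs were recruited at office meetings (Recruitment {15}), so colleagues may start close together. The 6-month lag puts many colleagues' index visits before release. An untrained colleague without coaching, co-management or eConsult would not perform like a treated PCP. The article may also condense a fuller release procedure.

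Most of this stands as a limit on size. It does not remove the conflict: the condition actually written is individual, and no office-level condition appears.

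Two supporting statements must also be read narrowly. "the exact timeline will differ between PCPs based on factors such as their patient population" belongs to a sentence about intervention PCPs, so the Fig. 2 legend carries the point about staggered finishing. "The study team developed a combination of CDS tools that are implemented into each intervention" describes intervention offices; nothing says that delayed access would be switched on for a whole control office. Restriction by user is possible, though it would not contain lecture content or a pocket guide.

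A reader might infer that a third of control patients are exposed and that half or all of the effect spills over, giving 5.0 or 4.0 points and power of 0.65 or 0.47. The arithmetic is right, but the inputs have no basis in the document and disregard the lag. A reader might also take the Discussion to claim that contamination is ruled out; it claims only that it is limited.

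**Conclusion.** The concern holds as a defect in the release rule. As written, the rule allows intervention materials into a control office before that office's primary outcome data are complete, contrary to the stated purpose of office-level allocation. The document does not support saying that this has happened or that it will be large.

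The direction is toward no difference, so this route would not produce a false positive. The size is unknown. Under assumed effective dilution of 2.5% to 10%, power falls from 80.5% to between 78.5% and 71.8%. The planned margin above 80% is about half a percentage point, so even the mildest of these scenarios takes power below target. The change is worth making because the threat is avoidable and the remedy is specific.

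**What to change.** Make release conditional on the office: offer the tools to its routine-care PCPs only when the last enrolled patient of every participating PCP there has reached 6 months. If the full protocol already requires this, correct the article's wording to match.

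The cost is more than editorial. Control PCPs have been told that the intervention follows completion of their own patients, so early finishers would wait longer than they were led to expect, and the change has to be communicated while recruitment is underway.

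If any tools have already been released, record the release date for each office. Add a sensitivity analysis that excludes control patients whose index visit fell after release in their office, or that flags those whose 6-month window overlaps it. Exclusion loses some control patients, mostly those of slower-recruiting PCPs, so it should support the main analysis and not replace it.

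Do not simply censor control charts at the release date. Outcomes {12} allows 6 months so that providers have time to meet the indicators. Shortening that period in the control arm alone would lower control scores, especially on follow-up indicators, and favour the intervention.
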